## Abstract

**Background:**

Pregnant women and children are vulnerable to air pollution-related adverse health effects, especially those residing in low-resource and high-exposure settings like India. However, evidence regarding the effects of early-life exposure to air particulate matter (PM) on childhood growth/developmental trajectory is contradictory; evidence about specific constituents of PM, like heavy metals, is limited. Similarly, there are few Indian cohorts investigating PM exposure and the incidence of acute respiratory infection during infancy. This study protocol aims to fill these critical gaps in knowledge.

**Methods:**

We aim to establish a mother–child birth cohort through the enrolment of 1,566 pregnant women residing in two urban areas of central India. Antenatally, we will collect socioeconomic, demographic, and clinical information and details of confounding variables from these pregnant women, who will then be followed up until childbirth to assess their exposure to air PM. Biomonitoring will also be conducted to evaluate heavy metal exposure. At birth, pregnancy outcomes will be noted, followed by postnatal follow-up of live-born children until the first year of life to assess their achievement of growth/development milestones and exposure to pollutants. We will also estimate the incidence of Acute Respiratory Infections (ARI) during infancy.

**Discussion:**

This manuscript describes the protocol for an Indian mother–child air pollution birth cohort study that aims to generate comprehensive evidence regarding the adverse effects of early-life (i.e., both pre- and post-natal) exposure to air PM and its constituent heavy metals among Indian children. This study will provide an epidemiological basis for further understanding in this context. Finally, by reporting our carefully planned study methods/outcome measures, which are comparable to those of published and ongoing birth cohorts, we aim to serve as the starting point for similar cohorts in the future, which, when considered together, would generate enough evidence to facilitate context-specific policy-making and development of appropriate prevention and mitigation strategies.

## Introduction

1

Air pollution is the most significant worldwide threat to human health and life expectancy, with 7 million global deaths being attributable to its exposure (1, 2). The United Nations Environment Programme (UNEP) reported that the vast majority of people worldwide reside in places where the concentration of particulate matter (PM) pollutants in the air exceeds the stringent permissible limits prescribed in the 2021 air quality guidelines of the World Health Organization (WHO) (3, 4). People living in India and other low- and middle-income countries, particularly pregnant women and children, are at significantly higher health risk (5–7). Therefore, the WHO– United Nations Children’s Fund (UNICEF)–Lancet Commission, in its 2020 report focussing on the future of the global child population, has stressed evidence generation and subsequent interventions to safeguard the health of children, especially in high pollution exposure settings, to expedite the fulfillment of the 48 child-related Sustainable Development Goal (SDG) indicators (8, 9).

Air pollution adversely affects pregnancy, fetal growth, and development (10–12). However, evidence regarding the effects of early-life (i.e., pre- and post-natal) exposure to air particulate matter on the childhood growth trajectory is contradictory. Some studies demonstrate an increased relative risk of childhood stunting, wasting, and being underweight (13–15). At the same time, others have also reported a higher risk of childhood obesity and raised body mass index (BMI) (16, 17). Even among infants, published evidence is contradictory. For example, a Colorado-based prospective cohort study reported higher adiposity among exposed infants at the 5th-month follow-up (18). Similar results were reported by a Chinese birth cohort (19). In contrast, a cohort study from Ghana reported lower length-for-age (stunting) and weight-for-length (wasting) z-scores among exposed infants (15). On the other hand, a recent randomized trial conducted in four low- and middle-income countries that substituted biomass burning with clean cooking fuel, leading to a reduction in antenatal personal exposure levels, reported no difference in the risk of stunting in infants (20). Therefore, further research is required to provide confirmatory evidence. This ambiguity in evidence might be because few studies have investigated the differential effect of chemical constituents of particulate matter, which are a heterogeneous mixture of multiple components with varying toxicity profiles (21). Particularly, there is a paucity of longitudinal research investigating the association between early-life exposure to multiple heavy metals and aberrations in childhood growth or development (22, 23). Considering the magnitude of the public health burden posed by air pollution and child growth/developmental abnormalities in low- and middle-income countries such as India (24), where annually more than 250 million under-five children fail to attain their optimum developmental potential (25), this study protocol aims to generate comprehensive evidence in this context to complement the limited India-specific evidence published so far (26–28).

Another adverse effect of prenatal air pollution exposure is the alteration of immune mechanisms in children (29–31), which can increase the risk of infectious diseases such as acute respiratory infections (ARIs). Evidence supporting this link is mainly based on studies conducted in high-income countries (32). The burden of childhood ARI is enormous in India, which is one of the top 15 countries globally in terms of the prevalence of ARI and subsequent childhood mortality, with 0.4 million under-five children dying annually from ARI-related diseases (33). However, Indian evidence on air pollution-induced childhood ARI is mainly limited to cross-sectional surveys or ecological retrospective data analysis. Further, these studies have used proxy measures such as questionnaire data to elicit either household exposures (34, 35) or ambient air pollution (36, 37). Thus, considering these knowledge gaps, this study protocol also focuses on identifying the association of variation in the incidence of ARI till one year of age among children exposed during early life to different levels of air PM and its heavy metal content.

## Aims and objectives

2

We aim to establish an urban mother–child birth cohort in central India. The data collected from this cohort will enable us to understand the health burden posed by early life exposure (i.e., pre- and post-natal) to air PM and its heavy metal composition in Indian children and the role of such environmental exposure in the multifactorial aetiology of our chosen study outcomes. The specific objectives being addressed in this research are:To investigate the variation in achievement of growth/developmental milestones during the infancy period of children attributable to different levels of early life exposure to air pollutionTo assess the incidence of acute respiratory infections during the infancy period of children attributable to different levels of early-life exposure to air pollutionTo find the association of exposure to selected heavy metals (as represented by blood concentration) among pregnant women /children with assessed morbidity outcomes of children.

## Materials and methods

3

During the drafting of this manuscript, details were reported as per the STROBE checklist, which was modified to suit requirements specific to the protocol of cohort studies (see Supplementary material).

### Study design

3.1

This is the protocol for a population-based prospective cohort study. During the first phase of this study, which will be implemented over three years, we will establish the mother–child birth cohort and conduct regular follow-ups for exposure and clinical assessments of study participants during the antenatal and 1-year postnatal period (see Figure 1). In the next phase, the established cohort will be followed up annually by securing further funding.

**Figure 1 fig1:**
[figure not shown]
Overview of activities to be conducted in the study (Activities under the study are listed on each row and the timing of each activity is indicated by a tick mark in the cells corresponding to the column headings showing the phase of study such as enrolment, gestational follow-up, post-birth and month-wise follow-up (FU) in the infancy period. Ambient air particulate matter/heavy metal assessment and land-use regression (LUR) modeling will be done over the entire study period and have been shown using arrows. ANC, antenatal care; APGAR, scoring given to child after birth based on appearance, pulse, grimace, activity, and respiration; ARI, acute respiratory infection; HC, head circumference; LUR, land use regression; MAC, mid-arm circumference; NICU, neonatal intensive care unit; PM, particulate matter).

### Study setting

3.2

The cohort population will be enrolled within the boundaries of urban local bodies (municipal corporations) of two selected cities (Bhopal and Ujjain) of Madhya Pradesh (MP), a large province located in central India (see Figure 2). The process of finalizing these two cities to establish the cohort has been detailed in Supplementary material (Data Sheet 1). MP is a large province with a total population exceeding 72 million (38), of which around 25% reside in urban areas (39). MP has thirty-two cities, with Bhopal and Ujjain ranking as the second and fifth most populous cities in the province, respectively (40). The child population accounts for 12.02 and 11.45% of the total population of these two cities, respectively (41, 42). The average literacy rate of the total population (Bhopal: 83.47% versus Ujjain: 84.43%, both of which are at a higher level than the Indian average of 74.04%) and proportion of slum population (Bhopal: 26.68% versus Ujjain: 23.32% both of which are at a higher level than the Indian average of 5.41%) in these two cities are comparable, highlighting that the socioeconomic scenario of these two cities are similar (41, 42).

**Figure 2 fig2:**
[figure not shown]
Map showing the location of study cities the image shows clockwise the map of India with the location of the central Indian province of Madhya Pradesh demarcated in green, inset of Madhya Pradesh showing the location of study cities- Bhopal and Ujjain (This image was developed by the research team in the QGIS software (Version 3.28.15). The India map with state and provincial boundaries and point location of Indian District Head Quarters (indicating location of cities) was retrieved from the survey of india- administrative boundary database available at https://onlinemaps.surveyofindia.gov.in/Digital_Product_Show.aspx).

### Study population

3.3

Consenting pregnant women (*n* = 783 from each city), aged ≥ 18 years, with documented gestational age less than or equal to 16th week, who have been primarily residing in the study cities for at least the past year (and have no imminent plan to shift residence for more than a continuous period of one month away from their current address during the study period) will be enrolled. We will exclude pregnant women who have a history of using any assisted reproductive technology or who have been diagnosed with a high-risk pregnancy where complications are anticipated (43). We will also exclude pregnant women with occupation or lifestyle factors that are reported by previous studies to be sources of exposure to high levels of PM (44–46). Women with pregnancy loss, preterm birth, and term neonates with birth asphyxia and diagnosed congenital anomalies will be identified using relevant records and withdrawn from further follow-up. Details of operational definitions to be used for excluding participants at the time of enrolment and during follow-up phases have been described in Supplementary Table S1.

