##### Pregnant women

3.4.2.1

In the first (baseline) visit to households of eligible and consenting pregnant women, the detailed residential address (including contact details and geographic coordinates), as well as details of the participant and her household members, will be collected at the time of enrolment. Briefly, we will collect information on age, education, occupation, lifestyle factors, medical history (including details of current/past pregnancy and prescription drug use), and relevant family history from the pregnant women. The maternal height and weight will be recorded at the baseline visit. Detailed data about previous pregnancies (if any) will include parity status, birth intervals between consecutive births, and history of anemia/malaria/urinary tract infection/other infections/any other complications in a past pregnancy. In addition, the demographic details, socioeconomic characteristics, water, sanitation, hygiene, and environmental factors related to her household will be collected. The enrolled pregnant women will be followed up once in each trimester in the remaining period of gestation to collect information regarding the occurrence of spontaneous abortion/miscarriage and the details of scheduled antenatal check-ups undergone by the pregnant women. We will note their preference for a hospital/healthcare facility where they would opt for childbirth.

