A limitation of this exposure-response cohort is the potential of missing personal exposure information in the first trimester. Considering operational feasibility, the 16^th^ week was chosen as the cut-off for pregnant women’s enrolment and the start of exposure assessment in the antenatal period. Previous research has shown that most women in India report their first antenatal care visit within a median time of 16 weeks of gestation, and only 19.6% of pregnancies are detected and registered within the first trimester (125, 126). Hence, it is likely that we will be enrolling most of our pregnant participants in the gestational period of the 12th -16th week, and our field-data-based exposure assessment will fail to account for the complete picture of first-trimester exposure. This can be a significant limitation since it is plausible that the sensitive window for exposure in this context can be during the first trimester. Data analyzed from the INMA Spanish birth cohort showed that the z-score for length at the 6th month of the child’s age reduced by 6% for every 10-μg/m^3^ increase in antenatal NO_2_ exposure during the first trimester (127). Block and Calderón-Garcidueñas (128) also stated that first-trimester exposure to organic constituents of PM, such as polycyclic aromatic hydrocarbons, had a maximal effect on fetal growth when compared with later exposures. This limitation affects birth cohorts in low- and middle-income countries in Asia and Africa. For example, a rural Ghanaian pregnancy cohort investigating air pollution and childhood growth trajectory enrolled pregnant women at or before the 24^th^ week of gestation (15). Authors would have been facing similar constraints as us since the median time to first visit for antenatal care among African women has been reported to be 5 months (129).

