We have attempted to overcome this limitation by incorporating past exposure open-access data (such as CPCB ground monitoring stations/satellite-based estimates) of PM_2.5_ into our constructed LUR models. Previous studies have used this method. For example, the recently published Californian population-based prospective pregnancy cohort study (MADRES) enrolled pregnant women with a gestational age of less than 30 weeks and obtained air pollution exposure information using data from the United States Environmental Protection Agency Air Quality System to model daily participant exposure beginning from 2 years before pregnancy (130). However, using only LUR modeling-based exposure assessment suffers from ecological fallacy (131). Final estimation is highly dependent upon the density of monitoring stations from which PM data can be used to train the models and the granularity of data for predictor variables and, thus, cannot accurately differentiate between individual-specific exposure, particularly when their residential addresses are clustered close together (132, 133). Hence, data triangulation by adding personally measured and biomonitoring data would increase confidence in the overall exposure assessment (134). We have thus adopted a multi-pronged strategy to estimate the study participants’ accurate exposure information.

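### Residence before enrolment is fixed only at city level and the article describes no address history, so modelled first-trimester PM may be placed at the wrong address for women who moved within the city after conception

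*Protocol article*

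**What the plan says.** Section 3.3 (Study population) sets two residence conditions on different units. Looking back, the unit is the city: women must have been "primarily residing in the study cities for at least the past year". Looking forward, it is the address: they must "have no imminent plan to shift residence for more than a continuous period of one month away from their current address during the study period". Women may enrol "with documented gestational age less than or equal to 16th week".

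Section 3.4.1 (Exposure data collection) assigns LUR-modelled PM2.5 and PM10 to each woman from the geocode of her residence. It adds personal measurement once per trimester after enrolment, partly to allow for mobility. Section 3.4.2.1 (Pregnant women) places the collection of "the detailed residential address (including contact details and geographic coordinates" at the baseline visit. No other address is described. Section 3.4.2.3.1 lists daily, monthly and annual mean PM at the participant's location as main exposures.

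The Discussion (section 4) expects that "it is likely that we will be enrolling most of our pregnant participants in the gestational period of the 12th -16th week". It concedes that field measurement will therefore miss part of the first trimester, and regards that trimester as a plausible sensitive window. Its remedy reads: "We have attempted to overcome this limitation by incorporating past exposure open-access data", namely into the LUR models.

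**The concern.** Historical PM data correct the time of exposure but not the place. For the remedy to give a woman her own first-trimester value, the geocode must be where she lived in those weeks. The look-back rule does not secure this: a woman who changed neighbourhood at week 8 is eligible. The article also describes no record from which her earlier address could be recovered.

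What is at stake is the within-city spatial contrast in the window that the authors single out. Section 3.6 plans monthly mean exposures and a distributed lag model over preceding periods, so early months enter the analysis in their own right. Misplaced early exposure would tend to weaken the first-trimester spatial estimate. Annual means that reach back before enrolment carry the same error. An address that was not asked for at baseline is hard to reconstruct at analysis.

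**Working it through.** The plan states no figure on this point, so there is none to reproduce. The check has two parts.

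**1. The sections side by side**

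- Unit of the look-back rule: city (3.3).
- Unit of PM assignment: residence geocode (3.4.1).
- Address described: one, at enrolment (3.4.2.1).
- Expected enrolment: mostly weeks 12 to 16 (section 4), so most or all of the first trimester is already past.
- Source of PM for that trimester: past data in the LUR model (section 4).
- Tool for mobility: personal sensors, after enrolment only (3.4.1).

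Followed as written, the article places a recent mover's first-trimester PM at her enrolment address. For her, the calendar weeks and the city are right and the location within the city is wrong.

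**2. Size, under stated assumptions**

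Inputs, none of them in the documents:

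- m, the share of women who moved within the city between conception and enrolment: assumed 2 to 20%.
- rho, the correlation of modelled PM between old and new address: assumed 0 to 0.8.
- f, the share of the trimester a mover spent at the old address. With moves spread evenly over weeks 0 to 16 and a 13-week trimester, f = (13/16) x 0.5 + (3/16) x 1 = 0.41 + 0.19 = 0.59, taken as 0.6. For enrolment at week 12 the same reasoning gives 6/13 = 0.46, so 0.6 is not a low value.

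For a mover, true exposure is f x old + (1 - f) x new, and assigned exposure is new. With equal variances, the slope of true on assigned is f x rho + (1 - f) = 1 - f(1 - rho). Over all women:

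attenuation = 1 - f x m x (1 - rho)

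The information retained is about the square of this. The square ignores the smaller variance of an exposure averaged over two addresses, so it slightly overstates the loss.

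Central case, f = 0.6 and rho = 0.5:

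- m = 5%: 1 - 0.6 x 0.05 x 0.5 = 0.985; squared 0.970; loss 3.0%.
- m = 10%: 1 - 0.6 x 0.10 x 0.5 = 0.970; squared 0.941; loss 5.9%.

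Loss over the assumed range, f = 0.6:

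| m | rho = 0.8 | rho = 0.5 | rho = 0 |
|---|---|---|---|
| 2% | 0.5% | 1.2% | 2.4% |
| 5% | 1.2% | 3.0% | 5.9% |
| 10% | 2.4% | 5.9% | 11.6% |
| 20% | 4.7% | 11.6% | 22.6% |

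The loss is small unless moves are common or the two addresses are nearly unrelated in PM. The formula assumes that moving is unrelated to outcome. If it follows socioeconomic status, the error may be differential, and the formula does not then give its size or direction.

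**The case against.** The strongest reply is that the article never says the enrolment address is used for back-assignment. Section 3.4.1 speaks only of residence geocodes, and the baseline form, eligibility checklist and exposure questionnaire are not shown. A residential history is the kind of item an article leaves to its forms. This stands as a limit on certainty: back-assignment to the enrolment address is inferred from three sections read together. It does not remove the point. Section 3.3 fixes the look-back unit explicitly, and the Discussion offers its remedy without the condition it depends on.

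The authors also disclose that first-trimester data are incomplete and that LUR separates clustered addresses poorly. This stands in part: short moves matter little. But what they disclose is missing measurement and coarse modelling, not a change of address before enrolment.

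Four stronger readings are tempting and are not supported:

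- A reader might infer that the study's sample of 571 pairs shrinks by the percentages above. Section 3.3.1 sizes that number for stunting under long-term PM2.5 exposure, not for a first-trimester spatial effect.
- A reader might take the worst case, with unrelated addresses and the whole trimester at the old one, as the expected loss. Nothing in the documents supports either value.
- A reader might combine the cited median week of first antenatal visit with the statement that "only 19.6% of pregnancies are detected and registered within the first trimester" to get the share of women without a first-trimester personal reading. These are separate literature figures, and neither describes this cohort's enrolment.
- A reader might suppose that addresses are right in later windows. Section 3.3 excludes only women with an imminent plan to move, so unplanned later moves remain possible.

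**Conclusion.** The point holds in a limited form. As the article describes it, pre-enrolment PM has the right time and the right city, but possibly the wrong neighbourhood, for women who moved within the city between conception and enrolment. The comparison between the two cities is unaffected, because a year in the city is required.

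The likely cost is modest: about 3 to 6% of the information on the within-city first-trimester effect in the central case, and more only if moves are more common or PM at the two addresses is nearly uncorrelated. All three inputs are assumptions. The conclusion also rests on no unshown form recording earlier addresses for use in exposure assignment. This is a worthwhile improvement rather than a threat to the study; the reason to act is that the information is cheap at baseline and hard to recover later.

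**What to change.** At the baseline visit, record each address and move date since the last menstrual period, preferably over the past year so that annual means are covered too. Geocode these addresses and assign first-trimester and annual PM as time-weighted LUR values over them. Add a sensitivity analysis restricted to women at one address since conception. Leave the city-level eligibility rule as it is. If a form already collects this history, one sentence saying that it is used for exposure assignment settles the point.

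The cost is one or two questions, some extra geocoding and a minor recall burden. Enrolment numbers do not change.
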